## 8. Data Analysis

### Analysis Plan

**Primary Outcome:** The primary outcome is CRC screening within the 6 months following randomization (yes/no). We will use electronic data to measure outcomes, which we previously demonstrated as highly valid for accurately capturing CRC tests. We will report the number and percent screened by randomization group. Generalized linear models with logit link and robust variance estimator will estimate the probability of screening. We will use predictive margins based on these logistic models to estimate differences in screening rates between randomization groups. Models will adjust for age, sex, race/ethnicity, education, and screening history prior to randomization. With a targeted enrollment of 1150 participants, we will have 80% power to detect a 10% net difference in CRC screening uptake among randomization groups.

**Secondary Analyses** will explore whether the effect of incentives on screening uptake differs by race/ethnicity, Medicaid coverage, income, education, sex, and history of prior CRC testing. Interaction terms between these variables and the intervention group will be included in multivariable models, and Wald tests will be used to assess the overall significance of effect modification.

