#### 4. Study Design

We propose to conduct a 3-arm randomized controlled trial to compare the effectiveness of an automated mailed fecal-testing program (**Arm 1 Mailed**) to two types of conditional monetary incentives provided upon completion of CRC testing: (1) a guaranteed financial incentive (\$10) (**Arm 2 Mailed plus Monetary**) or a probabilistic 1 in 10 chance of \$50 (**Arm 3 Mailed plus Lottery**). Our primary outcome will be completion of CRC testing at 6 months (defined as any type of recommended CRC test: FIT, colonoscopy, or flexible sigmoidoscopy). The primary analysis will test for difference in completion rates among randomization groups. Secondary analyses will explore differences (effect modification) in the effect of incentives on the primary outcome by race, ethnicity, and Medicaid subgroups.

Patients aged 50-75 as of January 1, 2017 and enrolled in 1 of 21 Western Washington KPWA Medical Centers will be eligible if they are not current for CRC screening, defined as no evidence in electronic health data (EHR and claims data) of fecal testing in the prior 12 months, no colonoscopy in the prior 9 years, and no flexible sigmoidoscopy in the prior 4 years. The clinics have more than 110,000 age-eligible patients and more than 34,000 are not current for CRC screening. Patients with a history of CRC or inflammatory bowel disease will be excluded. We will also exclude patients already participating in the ongoing SOS trial.

We will oversample from non-white and Hispanic groups and those with Medicaid coverage to ensure that at least two-thirds of the sample meets one or both of these criteria. KPWA has race and ethnicity data on 93% of patients in this age category, with almost 10,000 non-white or Hispanic patients who are overdue for CRC screening. At KPWA, almost 72% of white members aged 51-75 are current for CRC screening, while comparative rates among Asian, Black, and Native American members are 66-69%, with lower rates among Hispanic (64%) and Pacific Islander (61%) members, and patients with Medicaid insurance (55%).

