We will send letters to 5000 potentially eligible patients describing the study with a brief survey to collect sociodemographic information and confirm eligibility. Questions will be from the main SOS study and are based on the Preventive Health model that predicted screening in our main SOS and other studies, asking about self-efficacy, pros and cons of fecal testing, social influence, and “defensive information processing” (e.g., “I like to ignore the fact that I could get cancer”), which specifically addresses avoidance and inattention to screening. We will include a \$2 bill with the survey (based on evidence that this increases participation rates) to thank recipients for their time.

Based on our prior SOS ARRA Supplement (testing adherence to 3 types of fecal test kits), we expect 29% to return the survey and 23% to be eligible and enrolled, with a target enrollment of 1150 participants (two-thirds non-white or Hispanic and one-third Medicaid [white or non-white]). We will use a computer-based randomized sequence generator to assign patients to: (1) Mailed; (2) Mailed plus \$10; or (3) Mailed plus Lottery. Randomization will be stratified by history of prior CRC testing (yes/no based on electronic data), white vs. non-white race or Hispanic, or Medicaid status (yes/no) to ensure balance by these key characteristics. The randomization sequence will be concealed to everyone except the study programmer. Outcomes will be blinded until data collection is complete.

A second set of 5000 potentially eligible patients will receive mailings as described. Additionally, Kaiser Permanente Washington Health Research Institute’s (KPWHRI) Survey Research Program staff will conduct one reminder call to patients who do not return a survey after 14-21 days (approved by the KPWHRI Institutional Review Board on 6/12/2017). When respondents are available, the caller asks if they received the survey and if they have any questions. The patient may request another packet be mailed or refuse participation in the study at that time. The caller will ask for the survey to be returned within two weeks. When another person answers but the patient is not available, the caller leaves a message that they are calling from KPWHRI about a study and requests the best time of day to call again. If the caller receives an answering machine, a voicemail is left with a phone number to request a new questionnaire.

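### Medicaid status is used to stratify randomization but is missing from the primary model's covariates: a small, conservative loss of precision that one added term removes

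*Protocol*

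**What the plan says.** Section 4 (Study Design) sets out the stratification: "Randomization will be stratified by history of prior CRC testing (yes/no based on electronic data), white vs. non-white race or Hispanic", followed by "or Medicaid status (yes/no) to ensure balance by these key characteristics". The data collection table in Section 6 also marks insurance type as a stratification variable.

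Section 8 (Analysis Plan, Primary Outcome) specifies the model: "Generalized linear models with logit link and robust variance estimator will estimate the probability of screening". Differences between arms come from predictive margins, and the covariates are listed: "Models will adjust for age, sex, race/ethnicity, education, and screening history prior to randomization".

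Race/ethnicity and prior screening, two of the factors named in Section 4, appear in that list. Medicaid status does not, and no reason is given. Its only analytic role in Section 8 is as an effect modifier: "Secondary Analyses will explore whether the effect of incentives on screening uptake differs by race/ethnicity, Medicaid coverage, income".

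**The concern.** An analysis should normally reflect how participants were randomized. Stratifying on a prognostic factor removes chance imbalance on it, so the treatment contrast varies less from trial to trial. A model without the factor does not see this. Its residuals still contain the variation due to the factor, and a robust variance estimator does not remove it. The reported standard error then exceeds the true one, confidence intervals are a little too wide, and the test rejects a little less often than its nominal level.

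What is at stake is a small amount of precision. It is worth a comment because the stated power has little slack, the covariate list is written out in the protocol, and the missing variable is one the trial must already hold in order to randomize.

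**Working it through.** **Inputs from the protocol**
- Three arms ("We propose to conduct a 3-arm randomized controlled trial") and 1150 participants. Allocation is not stated; 1:1:1 is assumed, giving 1150/3 = 383.3 per arm.
- Power claim: "With a targeted enrollment of 1150 participants, we will have 80% power to detect a 10% net difference in CRC screening uptake".
- Planned Medicaid share of about one-third, from Section 4: "two-thirds non-white or Hispanic and one-third Medicaid [white or non-white".

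**Inputs that must be assumed**
- Two-sided alpha of 0.05 for each pairwise comparison, and the control rate. Neither is stated.
- The gap d in 6-month uptake between Medicaid and other participants. The protocol does not give it; 5 to 17 points is used. The upper value borrows the difference between 72% and 55% in Section 4, which measures something else (see the objection).

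**Step 1: the plan's own figure.** For 45% against 55%, with pooled variance under the null:
- SE under the null = sqrt(2 × 0.25/383.3) = 0.0361; under the alternative, sqrt(2 × 0.2475/383.3) = 0.0359.
- z = (0.10 − 1.96 × 0.0361)/0.0359 = 0.81, so power = 79.2%.

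Control rates of 35% to 55% give 79.2% to 80.8%. The stated 80% is reproduced.

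**Step 2: effect of the omission.** With Medicaid share f and overall uptake p:
- Share of outcome variance due to Medicaid: R² = f(1 − f)d²/[p(1 − p)].
- Overstatement of the SE when Medicaid is balanced by design but not modelled: 1/sqrt(1 − R²) − 1.
- Actual alpha: 2Φ(−1.96/sqrt(1 − R²)).
- Power, with S = 0.0361 × sqrt(1 − R²): omitted, Φ[(0.10 − 1.96 × 0.0361)/S]; included, Φ[0.10/S − 1.96].

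At f = 1/3 and p = 0.5:

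| Gap d | R² | SE overstated by | Actual alpha | Power, omitted | Power, included | Gain (points) |
|---|---|---|---|---|---|---|
| 5 points | 0.22% | 0.11% | 0.0497 | 79.10% | 79.16% | 0.06 |
| 10 points | 0.89% | 0.45% | 0.0490 | 79.18% | 79.43% | 0.25 |
| 17 points | 2.57% | 1.31% | 0.0471 | 79.38% | 80.10% | 0.72 |

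Worked line for 17 points: R² = 0.2222 × 0.0289/0.25 = 0.0257, and 1/sqrt(0.9743) − 1 = 0.0131. Using p(1 − p) = 0.24 instead gives R² = 2.7% and an overstatement of 1.4%, the upper end quoted.

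A wider grid (Medicaid share 10% to 50%, gap 5 to 25 points) gives an SE overstatement of 0.05% to 3.3% and a power gain of 0.03 to 1.8 points.

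**Step 3: simulation.** The planned analysis (logistic model, predictive margins, robust variance) was run on 12,000 simulated trials per scenario. The simulation assumed blocks of six within strata, one-third Medicaid, a 17-point gap, and race and prior testing as the other covariates.

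| Model | Mean reported SE | Empirical SE | Type I error | Power at 10 points |
|---|---|---|---|---|
| Medicaid omitted | 0.0352 | 0.0347 | 0.047 | 81.3% |
| Medicaid included | 0.0347 | 0.0346 | 0.049 | 82.1% |

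The estimate varies by the same amount under both models; only the reported SE changes, by 0.0352/0.0347 − 1 = 1.4%. Bias was 0.0005 or less under both. The simulation error of a rejection rate near 0.05 is sqrt(0.05 × 0.95/12,000) = 0.002, so both type I error rates are compatible with the calculated values.

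**The case against.** The strongest objection is that nothing of consequence is lost. The error is conservative, the stated power is reproduced without Medicaid, and under 1 point of power would rarely change a conclusion. That stands, and it limits the point to a minor one.

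The size is also uncertain, and probably towards the low end. A reader might infer from Section 4 that Medicaid participants will trail by 17 points. The protocol does not support that. The figures of 55% and almost 72% compare Medicaid patients with white members, not with non-Medicaid patients, and they describe being up to date in the general membership. Everyone enrolled here is overdue, and every arm is mailed a FIT. The nearest evidence, Table 1 in Section 3, shows a 12-point difference by race/ethnicity under usual care (29% against 17%) shrinking to 1 point with automated mailing (51% against 50%). That is race and 2-year adherence, so it is only indirect, but it warns against carrying a usual-care gap into this trial. The existing covariates may also absorb part of any Medicaid effect.

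Other stronger readings do not hold:
- Medicaid patients do not have the lowest screening rate in the protocol. Theirs is the lowest only among the health-plan rates in Section 4; Table 1 reports 17% in another group.
- Complete Medicaid data are not promised. Section 6 says only that the last recorded insurance type is used.
- Using Medicaid as an effect modifier in secondary models does not make the primary model wrong. Income has the same role and is also absent from the primary list.

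The mechanism has conditions too. No block size or method is given, and the argument assumes that stratification achieves the balance Section 4 claims. The wording there can also be read as one combined race-or-Medicaid stratum. Balance on Medicaid itself would then be only partial and the overstatement smaller, but Medicaid would still be missing from the model.

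**Conclusion.** The mismatch is real: a factor used in the randomization is left out of a covariate list that the protocol itself writes out. The consequence is a slightly overstated standard error and a slightly conservative test, without bias. With one-third Medicaid and a gap of 5 to 17 points, the overstatement is about 0.1% to 1.4% and the power gain from adding the term is below 1 point. Both the gap and the degree of balance are assumptions, and the true loss may be smaller. It would be wrong to infer that the primary test is invalid or the trial underpowered for this reason. This is a minor point and a free improvement. The SAP was not available for this review and may already include the term; if so, only the protocol wording needs to be aligned.

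**What to change.** In the covariate sentence of Section 8, insert *Medicaid status (yes/no, as used at randomization)* between education and screening history, and change nothing else. Race/ethnicity and screening history should not be collapsed to the binary forms used for stratification: Section 4 reports rates from 61% to almost 72% across racial and ethnic groups, so collapsing could lose more prognostic detail than Medicaid adds.

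The cost is one degree of freedom in a model for 1150 participants, using a variable that is already collected. The change should be made before outcomes are unblinded.

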Weekly, the SOS Disparities programmer will look for enrolled participants who have completed a FIT, flexible sigmoidoscopy or colonoscopy in the previous week. The study programmer will notify Survey Research Program

staff of results. Survey staff will then mail the participant an incentive based on their group assignment. A participant will have up to 6 months to complete a CRC screening test in order to receive an incentive.

We will not recontact people who return the survey and are ineligible and not collect any additional data from KPWA records beyond what we collect to identify the sample.

After all patients are randomized and have completed 6 months of follow-up, we will collect the following participant data from electronic records: CRC screening status, preventive visits (Pap smear last 3 years and mammogram last 2 years for women), body mass index, and diagnoses for calculating Charlson Co-morbidity scores. We will collect and keep data as described in the protocol on all enrolled participants, even if the participants choose not to return their FIT kit.

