## 15. Smart Options for Screening Survey

Survey # (preassigned)

Date Completed: \_\_\_\_\_

These questions are about your history of colorectal screening. You can skip any question you do not want to answer.

By returning this survey, I agree to participate in the Smart Options for Screening (SOS) program as described in the Information Sheet.

Please read each question carefully and put an x in the box that best describes your answer.

**The stool blood test, also known as a fecal occult blood test, is done at home to determine whether the stool contains blood. A sample of your fecal matter or stool is collected from 1 bowel movement and then the sample is returned in a small tube to a lab to be tested.**

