**These last questions are about you. Your answers will be combined with all answers.**

42. Do you consider yourself to be Hispanic or Latino?

- ☐ Yes
- ☐ No

43. What race do you consider yourself to be? (Record all that apply)

- ☐ American Indian /Alaska Native
- ☐ Asian
- ☐ Native Hawaiian or Pacific Islander
- ☐ Black or African American
- ☐ White
- ☐ More than One Race

44. How often do you need to have someone help when you read instructions, pamphlets, or other written materials from your doctor or pharmacy?

- ☐ Never
- ☐ Sometimes
- ☐ Always
- ☐ Rarely
- ☐ Often

45. What is your current marital status?

- ☐ Married
- ☐ Single/never married
- ☐ Divorced
- ☐ Living with partner
- ☐ Widowed
- ☐ Separated

46. What is the **highest** level of school that you have completed or the **highest** degree you have received?

- ☐ Less than high school
- ☐ High school degree or GED
- ☐ Some college, no degree
- ☐ Bachelor's degree
- ☐ Master's/Professional/Doctoral degree

47. What best describes your current paid work status? Please select one

- ☐ Working full-time
- ☐ Working part-time
- ☐ Retired
- ☐ Not working

48. During the past year, about how much money do you estimate members of your immediate household received from all sources such as work, Social Security, interest, investments, etc.? *Your best guess is fine!*

- ☐ Less than \$10,000
- ☐ Between \$10,000 and \$20,000
- ☐ Between \$20,000 and \$50,000
- ☐ Between \$50,000 and \$100,000
- ☐ More than \$100,000

**REMINDER CALL  
CONTACT SCRIPT (abridged)**

Contact

Hello. This is [INTNAME] calling from Kaiser Permanente Washington Health Research Institute.  
May I please speak with (RESPONDENT)?

*RESPONDENT NOT AVAILABLE*

Hello, this is [INTNAME] and I'm calling from Kaiser Permanente Research Institute about a study.  
Generally, are mornings, afternoons or evenings the best time to reach [RESPONDENT]?

*RESPONDENT AVAILABLE*

Hello, this is [INTNAME] and I'm calling from Kaiser Permanente Research Institute.  
Recently we sent you a survey in the mail asking questions about colon cancer screening  
We haven't received your survey, so we are calling to confirm that you got it and to see if you have any questions.  
Did you receive the **survey**?

IF NEEDED: DESCRIPTION OF PACKET/ENVELOPE

Do you have any questions about the **survey** or the study?

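### The primary model adjusts for education, a survey item participants may leave blank, so a standard fit would omit randomized people whose outcome is available from records

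*Protocol*

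**What the plan says.** Protocol section 8 (Analysis Plan) fixes both the primary model and its covariates. On the model it says "Generalized linear models with logit link and robust variance estimator will estimate the probability of screening". On the covariates it says "Models will adjust for age, sex, race/ethnicity, education", with past screening as the last item of the list. Differences between arms are then taken as predictive margins from that model. The same paragraph takes the outcome from electronic data, promises the crude number and percent screened by arm, and states 80% power for a 10-point difference with 1150 participants.

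Education is not a row in the table of EHR data elements under section 6 (Study Procedures). It appears only in the survey (section 15), where question 46 asks for the highest "level of school that you have completed". The head of the survey says "You can skip any question you do not want to answer". It also makes return of the form the act of agreement: "By returning this survey, I agree to participate in the Smart Options for Screening (SOS) program". Section 6 has staff confirm eligibility on the returned form and then randomize. It describes no step for recovering a blank question 46.

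On follow-up, section 6 says "We will collect and keep data as described in the protocol on all enrolled participants, even if the participants choose not to return their FIT". Section 4 stratifies randomization by prior CRC testing, race/ethnicity group and Medicaid status. Medicaid status is not among the covariates of the primary model.

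**The concern.** The protocol ties its primary estimate to a covariate that it lets participants withhold, although the outcome needs nothing from the survey. Someone who returns the form, is eligible and leaves question 46 blank is randomized, followed in the records and has an outcome. Standard logistic regression software nevertheless removes that person, because one covariate is missing.

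Two things are at stake. The first is size: the power statement uses all 1150 and mentions no allowance for missing covariates. The second is coverage. Predictive margins average over the people in the fit, so the adjusted difference would describe only those who answered question 46. The crude percentages reported beside it would have a larger denominator.

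**Working it through.** **Where each model variable comes from**

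- Age, sex, race/ethnicity, insurance type and past CRC screening status: rows of the EHR table in section 6.
- Education: survey question 46 only. Census block data are collected, but the protocol does not say they stand in for education.
- Outcome: electronic data (section 8).

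Education is thus the only covariate in the stated model that has no record-based source.

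**The plan's own power figure**

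Inputs from the protocol: 1150 participants, three arms, a 10-point difference, 80% power. Assumptions, because the protocol does not state them: equal allocation, two-sided alpha 0.05, one pairwise comparison without multiplicity adjustment, and an unadjusted two-proportion test.

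Per arm, n = 1150 / 3 = 383.3. With p = (p1 + p2) / 2,

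power = Φ{ [ |p2 − p1|·√n − 1.96·√(2p(1 − p)) ] / √(p1(1 − p1) + p2(1 − p2)) }.

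At 45% vs 55%, the least favourable case:

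- 0.10 × √383.3 = 1.958
- 1.96 × √0.5 = 1.386
- denominator √0.495 = 0.7036
- (1.958 − 1.386) / 0.7036 = 0.813, so power is 79.2%.

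The stated 80% is therefore reproduced. The total needed for a full 80% in this case is 3 × 392 = 1176, so 1150 has no slack at mid-range rates.

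**Effect of dropping blank rows**

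The documents give no rate of missing education, so the rates below are assumptions.

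- 5% missing: 1150 × 0.05 = 57.5, about 58 lost and 1092 left, n = 364.2 per arm.
- 10% missing: 115 lost and 1035 left, n = 345 per arm.

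| Rates compared | All 1150 | 5% missing | 10% missing |
|---|---|---|---|
| 30% vs 40% | 82.8% | 80.9% | 78.8% |
| 45% vs 55% | 79.2% | 77.1% | 74.9% |
| 50% vs 60% | 79.6% | 77.5% | 75.3% |
| 51% vs 61% | 79.8% | 77.7% | 75.5% |

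At 45% vs 55%, 1% missing gives 78.8%, 2% gives 78.4% and 20% gives 69.8%. If every randomized participant stays in the model, the first column applies.

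**Bias between arms**

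Section 6 places the return of the survey before randomization. Whether question 46 is blank is settled before the arm is known, so it cannot depend on the arm. Dropping those people leaves the arms comparable. What is lost is precision and coverage.

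**The case against.** The strongest reply is that the protocol nowhere prescribes a complete-case analysis, names no reduced analysis population, and may leave missing baseline covariates to a statistical analysis plan that is not shown. A reader might infer that the plan excludes these participants. The text does not say so; exclusion is what a default fit of the stated model does. This limits how the point may be put, but it does not remove it, because the skippable covariate is written into the primary model in the protocol itself.

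Other parts of the reply also stand:

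- The loss is small at plausible rates, and the rate is assumed. The power figures come from an unadjusted test, and the protocol does not show how much precision education would add to the adjusted model.
- Education is a pre-specified baseline variable and also a planned effect modifier in the secondary analyses, so wanting it in the model is reasonable.
- The crude percentages by arm, which need no covariates, will be reported in any case.

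Two stronger readings are tempting but unsupported. One is to add missing race/ethnicity to the loss, because section 4 says "KPWA has race and ethnicity data on 93% of patients in this age category". That figure describes the age-eligible membership. The invited sample is selected on recorded race, ethnicity and insurance (section 2), and survey questions 42 and 43 ask for race and ethnicity again, so 7% missing among participants does not follow. The other is that those omitted would mostly be people with low literacy or little engagement. That is conceivable in this population, but nothing in the protocol shows who skips question 46.

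**Conclusion.** The point holds in a limited form. The primary model contains a covariate that only the survey supplies and that participants may skip, while the outcome comes from records. Fitted in the standard way, the stated model would omit those who left the item blank.

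The comparison between arms would not be biased. The analysed sample would fall below 1150 and the adjusted estimate would no longer cover everyone randomized. At mid-range screening rates, power of about 79-80% would become about 77-78% with 5% missing and about 75-76% with 10%. At 30% vs 40% it would still be 80.9% with 5% missing. These figures rest on the assumed missing rates, equal allocation, two-sided 0.05 and a single unadjusted pairwise comparison. This is worth correcting because the correction is nearly free; it does not threaten the trial's validity.

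**What to change.** State in section 8 that the primary model includes all randomized participants. Adjust for age, sex and the stratification factors held in records: race/ethnicity stratum, Medicaid status and prior CRC testing. This also brings in Medicaid status, which is used to stratify but is absent from the stated model.

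For education, choose one of two options:

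- keep it in the primary model with a not-reported category, which is acceptable for a covariate measured before randomization; or
- move it to a sensitivity model.

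The cost is a sentence or two of text and no extra data. Moving education out gives up whatever precision it would add; the not-reported category largely avoids that.
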